### Sample size

The total number of women entered for screening will be determined by the CE positivity ratio on screening. A 50% positivity rate has been assumed with a total screen population of 3062 accounting for participant drop out of 2%. This will give a maximum sample size of 1500 randomised with 750 in each arm. The study is therefore powered to detect an 8% between group difference this has been pragmatically selected due to limited previous high-quality work in the area. There are three planned interim analyses after 100, 300 and 900 women have reached 28 weeks post randomisation. These analyses will assess for futility and be reviewed by the DMC. Prespecified stopping rules as documented in the statistical analysis plan will be applied.

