## Introduction

Recurrent miscarriage is an important cause of reproductive associated morbidity. Defined as the loss of two or more pregnancies, it has a population prevalence of up to 3%.^1^ It is research priority within reproductive health.^2 3^ A *Lancet* review series highlighted the ongoing uncertainty around the aetiology of recurrent miscarriage.^1^ It is hypothesised that chronic endometritis (CE) is a cause of recurrent miscarriage.^4^ In CE, there is asymptomatic inflammation of the endometrium mediated by infiltration of the endometrial stroma by plasma cells.^5^ CE remains of uncertain aetiology being differentially attributed to dysbiosis of the endometrial microbiota and the presence of pathological species within the endometrium.^6–8^ There is not consensus around the diagnosis of CE.^9^ Traditionally, CE has been diagnosed on histology through the identification of infiltrating endometrial plasma cells.^10^ Recently, this has been augmented using CD138 immunohistochemistry.^11^ While this has resulted in improved sensitivity, the diagnostic thresholds remain variable and the impact on therapeutic outcome varies dependent on the CD138 threshold set.^9^ Liu *et al* evaluated different diagnostic methodologies demonstrating a technique based on whole section density to have the lowest intraobserver and interobserver variability.^11^ The study also identified a density threshold based on the 95% CI with a differential prevalence of 22.2% in those with reproductive failure in comparison to 5% in fertile controls (p<0.01). McQueen *et al* assessed the effect of antibiotic treatment in a cohort of women presenting with recurrent miscarriage or loss of a single fetus>10 weeks gestation.^12^ Following treatment with antibiotics, a similar cumulative live birth rate (LBR) was seen in the CE group in comparison to controls (88% treated CE vs 74% without CE; p=0.215). A significant increase in per pregnancy LBR pre-treatment and post-treatment for CE was also seen (7% pre-treatment LBR vs 56% post-treatment LBR; p<0.001). Similarly, a retrospective cohort study assessing for the presence of CE demonstrated a marked improvement in LBR in those with CE resolution following antibiotic therapy (78.4% LBR in resolved CE vs 17.5% LBR persistent CE; p<0.001).^13^ Doxycycline is the most commonly reported antibiotic therapy used in the treatment of CE. A single course has previously been reported to achieve histological resolution in 92% of cases.^14^ These findings, however, remain limited by sample size and methodological concerns including lack of randomisation and lack of untreated controls. Despite this however, commercial testing is now available within the private sector.^15^ Given the combined limitations in pathophysiological and clinical understanding of the condition, a novel translation approach is required. In view of this, the Chronic Endometritis and Recurrent Miscarriage (CERM) trial was developed as a novel translation approach to better determine the role of CE in recurrent miscarriage and the potential for therapeutic intervention.

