#### Randomisation

Following a screen positive result for CE, women are eligible for randomisation provided they remain eligible based on the previous entry criteria, have not subsequently received a course of antibiotics, or had a delay of longer than 3 months since the biopsy was undertaken. Consent is further confirmed by a medical doctor, and randomisation undertaken by a member of the site research team using an online web application hosted by the WCTU. Block randomisation is performed in a 1:1 ratio, with Minimisation by age (<35 vs ≥35 years), number of previous miscarriages (≤3 vs >3) and site.

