### Alterations to study design since commencement

Initial establishment of the trial was on the basis of coprimary outcomes: ongoing pregnancy at 12 weeks at the end of the trial and livebirth ≥24 + 0 weeks gestation at the end of the trial, in the first or subsequent pregnancy. Like other clinical trials, the timeframe for recruitment has meant the trial has been heavily impacted by the COVID-19 pandemic. This has resulted in under-recruitment, with a lower-than-expected trial enrolment size falling short of the targeted 3062 screened and 1500 randomised. In view of this, the TSC unanimously agreed on 22nd November 2022 that, given a likely smaller than anticipated participant population, reduction to a single primary outcome of livebirth ≥24 + 0 weeks gestation at the end of the trial, in the first or subsequent pregnancy, was necessary to ensure statistical robustness. A formal protocol and REC amendment was made, and the change was approved by both the TSC and chair of the DMC.

Also because of the COVID-19 pandemic, a decision was made to allow consent to randomisation to be undertaken over the telephone (this previously required written consent). This was enacted to reduce hospital site visits and a REC amendment made.

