### Trial progress to date

This trial opened for recruitment on 19 December 2019 and closed to new registrations on 30 September 2022. The trial is currently in the follow-up period, and the study is expected to be completed by 30 April 2024.

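### The article still presents the trial as powered for an 8% difference on 1500 randomised, although recruitment closed short of 1500 and no revised figure is given

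*Protocol article*

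**What the plan says.** The Sample size section derives the randomised total from the number screened, using 50% positivity for chronic endometritis and 2% drop-out. It continues: "This will give a maximum sample size of 1500 randomised with 750 in each arm". The next sentence draws the conclusion: "The study is therefore powered to detect an 8% between group difference". It gives no target power, error rate or control-arm rate. It also does not say whether 8% is absolute or relative.

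The Abstract repeats the 3062 and the 1500 as expected maxima. End of trial lists follow-up of 1500 women first among the ways the trial can end.

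Two later sections change the picture. Alterations to study design since commencement reports under-recruitment, "with a lower-than-expected trial enrolment size falling short of the targeted 3062 screened and 1500 randomised". It adds that on 22 November 2022 the steering committee agreed to reduce the co-primary outcomes to one for that reason. Trial progress to date says the trial "closed to new registrations on 30 September 2022" and is in follow-up.

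**The concern.** The power sentence is in the present tense and rests explicitly on 1500 randomised. The same article says that number was not reached and that registration is closed. The protocol version described in Methods and analysis is dated 22 June 2023, about nine months after closure and seven months after the steering committee's decision. The shortfall is therefore a current fact, not superseded text. It led to a change of primary outcome, but the power statement that depended on the planned sample was left unqualified.

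What is at stake is how a neutral result is read. Set beside a claim of power for 8%, it invites the conclusion that a benefit of that size has been ruled out. The achieved sample may not be able to rule it out, and the article does not let the reader judge.

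**Working it through.** **Inputs from the article.** 3062 screened, 50% positive, 2% drop-out, 1500 randomised and 750 per arm (Sample size); 1:1 allocation (Randomisation); difference 8%, read here as 8 percentage points.

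**Inputs assumed because the article does not give them.** Two-sided 5% error rate; control-arm rate of the primary outcome between 40% and 70%. The planned analysis is a Bayesian logistic regression, so a fixed-sample two-proportion test is only a yardstick.

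**Step 1: the plan's own chain.** 1500 / 0.50 = 3000; 3000 / 0.98 = 3061.2, rounded up to 3062. In the other direction, 3062 × 0.50 × 0.98 = 1500.4. The planned numbers reproduce.

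**Step 2: power at 1500.** With V = p₀(1 − p₀) + p₁(1 − p₁) and p₁ = p₀ + 0.08, the standard error is √(V / n), with n per arm, and power ≈ Φ(0.08 / SE − 1.96).

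For p₀ = 0.60: V = 0.2400 + 0.2176 = 0.4576; SE = √(0.4576 / 750) = 0.0247; 0.08 / 0.0247 = 3.24; power = Φ(1.28) = 0.90.

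**Step 3: total needed for 80% power.** n per arm = (1.960 + 0.842)² × V / 0.08² = 7.849 × V / 0.0064, rounded up and doubled.

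| Control rate | V | Power at 1500 | Total for 80% power |
|---|---|---|---|
| 40% | 0.4896 | 88% | 1,202 |
| 50% | 0.4936 | 88% | 1,212 |
| 60% | 0.4576 | 90% | 1,124 |
| 70% | 0.3816 | 94% | 936 |

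Using a pooled variance under the null moves the last column only to 942–1,218.

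**Step 4: illustration below 1500.** The article gives no achieved total, so these sizes show the gradient and are not estimates of what was enrolled. At 1200, power for 8 points is about 80% to 89%, and the difference detectable with 80% power is 7.1 to 8.0 points. At 900, the size of the third planned interim analysis, power is about 68% to 78%, and the detectable difference is 8.2 to 9.3 points.

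**Step 5: missing primary outcomes.** The 2% is used up in Step 1, before randomisation. If 10% of 1500 were missing, 1350 would remain. At a 60% control rate, SE = √(0.4576 / 675) = 0.0260 and power is 87% rather than 90%. This input is minor.

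**The case against.** The strongest defence is that nothing was miscalculated and nothing is hidden. The planned numbers reproduce, and 750 per arm does give good power for 8 points under reasonable inputs. The article calls 1500 a maximum, and Trial setting calls it an initial aim. The shortfall is disclosed and was acted on by moving to one primary outcome. If the error rate had been split equally between the two co-primaries, which the article does not say, dropping one would offset a fall to roughly 1,240–1,270 randomised. Revised operating characteristics may sit in the full protocol or SAP, and credible intervals will show the lost precision.

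Much of this stands, and it limits the point. It does not rescue the sentence: the maximum is known not to have been reached, the disclosure is not linked to the power statement, and that statement is made in this article and not deferred elsewhere.

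Two stronger readings are tempting, and the documents support neither.

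- A reader might infer that power for 8% has gone. The achieved total is not given, and about 1,210 or more would still give roughly 80% across the assumed control rates.
- A reader might infer from the Introduction's "differential prevalence of 22.2% in those with reproductive failure in comparison to 5% in fertile controls" that the 50% positivity assumption was itself a cause of lost power. That figure concerns reproductive failure in general. The Sample size section lets positivity set the number screened, not the number randomised, and the article attributes under-recruitment to the pandemic.

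**Conclusion.** The point holds as an internal inconsistency: the article keeps a power statement whose stated basis, 1500 randomised, it elsewhere reports as not achieved. Power is below what 1500 would have given, but how far below cannot be established from the article. It states no numerical power against which a loss could be measured. The threshold of about 940 to 1,210 for 80% power depends on the assumed two-sided 5% test, an absolute 8-point difference and control rates of 40% to 70%. The design arithmetic, the outcome definition and the planned analysis are not in question here.

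**What to change.** In the Abstract and the Sample size section, label 3062 screened, 1500 randomised and the 8% difference as the original design target, and cross-refer to the section on alterations. Keep the design calculation and annotate it. Then state:

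- the number actually randomised;
- the assumed control-arm rate, and whether 8% is absolute;
- a modest allowance for missing primary outcomes;
- the resulting detectable difference, or the expected credible-interval width, which suits the Bayesian analysis better.

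Add one sentence saying that a credible interval which includes an 8-point benefit will not be read as excluding it.

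This is a text change needing no new data and no change to design or analysis. Its cost is that the stated detectable difference becomes less favourable than the present wording suggests.

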### Data analysis

Data will be analysed by intention to treat at randomisation. The treatment difference for the primary outcome will be assessed by deriving the posterior distribution of a Bayesian logistic regression model with a weakly informative prior distribution for all parameters. Although unlikely, in the event of missing data for primary outcomes of>10% imputation techniques will be used. The result for the primary outcome will be reported as the median value of the simulated ORs with the corresponding credible intervals. Secondary outcomes as previously outlined will be similarly assessed. The time-to-event (first pregnancy) analysis will be assessed using semiparametric proportional hazard regression. The following predefined subgroup analyses of the primary outcomes will also be assessed by age (<35 vs ≥35), number of previous miscarriages (≤3 vs >3), severity of CD138 expression and pattern of CD138 expression.

### AE management

AE will be collected to 30 days post-trial intervention, this may be either screening biopsy, treatment completion or secondary biopsy whichever comes later dependent on the participants trial arm. AEs captured elsewhere in the trial data do not require reporting, including those related to pregnancy outcome. In addition, common pregnancy related serious adverse events (SAEs) as seen in box 1 are exempt from SAE reporting but should be reported as AE. A causality assessment will be performed by a doctor for all SAEs and AEs. These will be assessed by the trial management group (TMG) and the DMC. SAEs and AEs thought to be related or unexpected will be reported to the Medicines and Healthcare Products Regulatory Agency) and Research Ethics Committee (REC), the sponsor and the chairs of the Trial Steering Committee (TSC) and DMC.

Box 1Adverse events (AEs) exempt from serious adverse event reporting but recorded as AEsAdmission to hospital for nausea and vomitingAdmission to hospital for headachesAdmission to hospital for raised blood pressure or pregnancy induced hypertensionAdmission to hospital for vaginal bleeding

### Monitoring

All clinicians involved in consent should have up to date Good Clinical Practice (GCP) training. Samples may be collected by those who fulfil this role in a clinical capacity. All involved will undergo a relevant programme of training. Site visits will be conducted where concerns arise. Data will be monitored for completeness and quality, where queries arise these will be escalated to the site involved.

A TMG comprising coinvestigators, allied experts, a patient public involvement advisor and the trial management staff will meet monthly to bimonthly to review the day-to-day running of the trial.

A TSC has been established comprising a group of independent experts covering all trial areas and lay members. The TSC will be responsible for protocol approval and review of any protocol changes, advising on aspects of trial conduct, monitoring trial progress and consideration of any recommendations from the DMC. They will meet not less than once a year. Any protocol modifications as agreed by the TSC will be submitted to relevant parties.

A DMC has been established comprising independent experts. They will ensure monitoring of outcomes and safety aspects during the trial.

An authorised representative of the sponsor has approved the final version of the protocol with respect to the trial design, conduct, data analysis and interpretation and plans for publication and dissemination of results.

### Integrated trial design

This trial uses an integrated adaptive approach. This allows facilitation of both assessing the core clinical outcomes but also the development of a concurrent sample and dataset for mechanistic evaluation should an effect be seen. It also allows better understanding of the aetiology of the condition including through the follow-up of those with a negative result. This integrated mechanistic clinical approach forms a model for a more economical approach to trial design in poorly understood conditions. Through more efficient use of resources, it allows the development of a holistic approach to disorder determination. A key hallmark of this design is the flexibility provided by the adaptive design and integration of sample banking. This ensures that a rigorous methodological approach is taken while still facilitating exploratory research. In fields such as this, which face the difficult challenges of a limited evidence base and disorder heterogeneity such approaches are likely to prove increasingly necessary.

### Patient and public involvement

The trial has been designed with the involvement of the Lily Mae Foundation, a charity supporting women who have lost a baby through miscarriage, stillbirth, neonatal death or medical termination. [name], cofounder of the charity, sits on the TMG. She has additionally led on the development of patient-facing materials.

### Alterations to study design since commencement

Initial establishment of the trial was on the basis of coprimary outcomes: ongoing pregnancy at 12 weeks at the end of the trial and livebirth ≥24 + 0 weeks gestation at the end of the trial, in the first or subsequent pregnancy. Like other clinical trials, the timeframe for recruitment has meant the trial has been heavily impacted by the COVID-19 pandemic. This has resulted in under-recruitment, with a lower-than-expected trial enrolment size falling short of the targeted 3062 screened and 1500 randomised. In view of this, the TSC unanimously agreed on 22nd November 2022 that, given a likely smaller than anticipated participant population, reduction to a single primary outcome of livebirth ≥24 + 0 weeks gestation at the end of the trial, in the first or subsequent pregnancy, was necessary to ensure statistical robustness. A formal protocol and REC amendment was made, and the change was approved by both the TSC and chair of the DMC.

Also because of the COVID-19 pandemic, a decision was made to allow consent to randomisation to be undertaken over the telephone (this previously required written consent). This was enacted to reduce hospital site visits and a REC amendment made.

## Ethics and dissemination

The trial will be conducted in full conformance with the principles of the Declaration of Helsinki, International Council for Harmonisation GCP guidelines and the UK Statutory Instrument Number 1031 that implements the Medicine for Human Use (Clinical Trials) Directive 2004 and subsequent amendments. Ethical approval for the trial has been obtained from the NHS REC Northwest-Haydock (REC reference: 19/NW/0462, REC approval date: 20/08/2019). The key ethical consideration of the trial revolves around the paradox of asking women who are eager to achieve successful pregnancy to avoid pregnancy for 3 months while undergoing trial procedures. To mitigate this, trial procedures will be kept to as short a period as possible. It is hoped the potential for gain minimises this paradox. All participants will provide written informed consent including for the biobanking of samples at the point of the screening biopsy. Telephone consent will subsequently be taken at the point of randomisation. The consent form is included within the online supplemental material.

10.1136/bmjopen-2023-081470.supp1Supplementary data

The trial will be reported in accordance with the Consolidated Standards of Reporting Trials guidelines.^20^ The trial will be published in an open-access peer reviewed journal with authorship agreed as per ICMJE requirements.^21^ The full protocol and trial findings will also be reported in the NIHR journals library. In addition, dissemination at national and international specialist conferences will be undertaken. Exploratory outcomes will be disseminated separately in open-access peer-reviewed journals to accommodate their more specialist nature.

### Trial progress to date

This trial opened for recruitment on 19 December 2019 and closed to new registrations on 30 September 2022. The trial is currently in the follow-up period, and the study is expected to be completed by 30 April 2024.
